**Methods:**

A prospective cohort study will be conducted in 41 health facilities and surrounding communities in Punjab, Pakistan. The primary objective of the study is to compare the 12-month contraceptive continuation rate for women who receive DMPA-SC with that for women who receive intramuscular depot-medroxyprogesterone acetate (DMPA-IM). The secondary objectives are to compare characteristics and experiences of participants who opt for DMPA-SC with those of women who opt for DMPA-IM, which must be administered by a health worker. Additionally, a sub-study is planned to assess how well women opting for self-injection of DMPA-SC adhere to standards for commodity storage, injection timing, injection technique and waste disposal.

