## Methods/design

### Study design

This will be a non-randomized prospective cohort study. We calculated the sample size necessary to detect a 10% difference in 12-month continuation rates between DMPA-SC and DMPA-IM users with 80% power at 0.05 level of statistical significance. Assuming equal preference for each injectable method, a 12-month continuation rate of 50% for DMPA-IM users, and a retention rate of 75% follow-up following the 4th injection (the equivalent of 12-months of contraceptive coverage), a total of 500 participants are needed in each intervention group. Thus, we anticipate enrolling a total of 1,000 women (500 DMPA-SC clients and 500 DMPA-IM clients).

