### Study setting and site selection

Pakistan’s administrative divisions include four provinces (Balochistan, Kyber Pakhtunkwa, Punjab, Sindh), two autonomous territories (Azad Jammu Kashmir, Gilgit-Baltistan) and a federal capital territory (Islamabad), which are further divided into districts, tehsils (sub-districts), and union councils (villages). Health sector governance was decentralized in 2010–11, with a constitutional amendment placing responsibility for health policy, financing and implementation with provincial authorities [24].

This study will be conducted in Punjab province where the modern contraceptive prevalence rate (mCPR) among married women is 27% [10]. One in six married women in Punjab has an unmet need for family planning, and demand satisfied by modern methods is 50% [10]. Mirroring national trends, the modern contraceptive method mix among married women is dominated by male condom use (28% of contraceptive users) and female sterilization (27%). Injectables contribute 6% of the modern method mix [10].

A total of 41 health facilities were selected as study sites across two districts of Punjab, Kasur and Khanewal. These districts were selected in consultation with the Government of Punjab to represent two of the three administrative regions of Punjab (Central and Southern) and based on the following criteria: mix of urban and rural populations, existing utilization of injectable contraceptives and functional government structures. The government-recommended districts of Kasur and Khanewal were endorsed by the project’s Steering Committee. Health facilities were purposively selected as study sites by study team members, in consultation with local authorities, to reflect variations in location (urban/rural), ownership (Department of Health, Population Welfare Department, private sector), and facility type (district headquarter hospitals, tehsil headquarter hospitals, rural health centers, basic health units, family health clinics, family welfare centers, and private clinics).

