### Support for family planning service provision

Study team members will visit each selected health facility to confirm staffing, availability of a family planning service delivery area with space for self-injection training, an appropriate storage space with at least three-month supply of family planning commodities (to mitigate risk of stock-outs during the anticipated enrollment period), and a secure location for storage of study documents. If a selected health facility is unable to demonstrate readiness for study implementation, an alternative of the same type may be identified in collaboration with local authorities. All family planning service providers at selected facilities will receive a three-day training, followed by supportive supervision visits, to ensure that they have the necessary knowledge and skills to counsel clients on a full range of contraceptive methods, screen clients according to the WHO’s Medical Eligibility Criteria (MEC), administer DMPA-IM, DMPA-SC, and effectively coach women to self-inject, calculate their reinjection date, and adopt proper waste management techniques. Community health workers serving populations in facility catchment areas will also receive a one-day training on DMPA-SC, MEC and injection techniques to enable them to support self-injection clients, and, together with male social mobilizers, support community engagement activities to generate awareness about the new family planning method and its availability in study districts. Study team members will conduct routine supportive supervision and monitoring visits to confirm continued readiness for family planning service provision and fidelity to counseling and service provision protocols. In the event that a facilities experiences a stock-out during the enrollment period, recruitment of clients will be paused at that site until commodities are supplied and readiness is again confirmed. Once enrollment targets are met, the study team will continue to monitor family planning service provision at these facilities but will not intervene in the management of commodities supplied by the Department of Health or Population Welfare Department.

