#### Participant recruitment and enrollment (January – June 2024)

After the client receives their contraceptive method of choice, health workers will provide each client receiving injectables with information about the study, inquire about interest/willingness to learn more about the study, and—if she agrees—obtain informed consent and record her contact information in an enrollment log. Clients providing informed consent to be contacted by study team members will be asked how they would like to be contacted (via telephone or home visit) and contact information recorded. At the end of each workday, health workers will then share enrollment details with study staff, who will contact the client in-person or by phone to confirm eligibility and consent and conduct intake interviews.

Enrollment limits proportional to average family planning client caseload will be set for each facility type, to ensure cohorts include participants from all levels of the health system.

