#### Data analysis

Characteristics (e.g. demographics, contraceptive history, reasons for methods choice, reproductive empowerment measured using a validated scale developed by MEASURE Evaluation [25], general self-confidence) and experiences of women enrolled in DMPA-SC and DMPA-IM study arms will be compared using *t* tests for continuous variables and chi^2^ tests for categorical variables. Differences in contraceptive continuation rates of DMPA-IM and DMPA-SC users will be compared at each follow-up point (6,9 and 12-month continuation rates) using Kaplan–Meier survival analysis methods and factors associated with risk of discontinuation analyzed using a Fine-Gray subdistribution hazard model.

Additional descriptive analyses of DMPA-SC user characteristics and experiences may include comparisons of the proportion of clients opting for DMPA-SC who successfully self-inject their first dose under the supervision of a provider; if assistance is sought for subsequent injections; what type of assistance is sought, and from who; and confidence in self-injection capacity.

DMPA-SC client adherence to storage, injection timing, and waste disposal standards will also be measured using descriptive statistics, with sub-analyses comparing differences in adherence based on household demographics, location and access to health services.

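### The pooled comparison of DMPA-SC and DMPA-IM users describes the sample fairly but cannot separate where DMPA-SC was taken up from who opted for it; a facility-stratified estimate should stand beside it

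*Protocol article*

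**What the plan says.** The secondary objectives (Abstract, Methods) are to "compare characteristics and experiences of participants who opt for DMPA-SC with those of women who opt for DMPA-IM". For this the Data analysis section says that characteristics and experiences of "women enrolled in DMPA-SC and DMPA-IM study arms will be compared using" t tests for continuous variables and chi-squared tests for categorical ones. It names no stratum, covariate or cluster term for facility, facility type, ownership, urban or rural location, or district. Location appears only in sub-analyses of adherence among DMPA-SC clients, and the Fine-Gray model concerns discontinuation.

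Four statements elsewhere bear on this:

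- Study setting and site selection: "A total of 41 health facilities were selected as study sites across two districts of Punjab, Kasur and Khanewal". They were picked purposively "to reflect variations in location (urban/rural), ownership (Department of Health, Population Welfare Department, private sector), and facility type".
- Study design: "This will be a non-randomized prospective cohort study". The Study population section leaves the product to the woman's choice. The target of 500 per group is an overall one.
- Participant recruitment and enrollment: "Enrollment limits proportional to average family planning client caseload will be set for each facility type". No limit by method within a facility is stated.
- Support for family planning service provision: in a stock-out, "recruitment of clients will be paused at that site until commodities are supplied and readiness is again confirmed".

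**The concern.** Sites picked to differ in setting, ownership and level will probably serve different women. If the DMPA-SC share also differs between sites, the two groups will differ on anything that varies by site, even where choice is unrelated to that factor inside every facility. The pooled test then responds to a mixture of two things: where DMPA-SC was popular, and which women preferred it when both products were on offer. For experiences, the service at the facility is mixed with the product itself.

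The article wants both answers. The Abstract says policymakers lack evidence on for whom to introduce DMPA-SC. The Background asks how and where self-injection may help, and names differences in user profiles as part of that question. One pooled contrast cannot tell the two apart.

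A second, related weakness is that ordinary t and chi-squared tests treat women from the same facility as independent observations.

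**Working it through.** **The plan's own figure.** The only computed figure is the primary sample size; none is given for this comparison. With 50% v 60%, two-sided 0.05 (sidedness assumed), 80% power and unpooled variance, n = (0.25 + 0.24) × (1.960 + 0.842)² / 0.10² = 385 per group, and 385 / 0.75 = 514. The stated 500 is within 3% of this. With 375 evaluable per group, power is 79.0%. The figure reproduces and the present point does not touch it.

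**Inputs.** From the protocol: 1,000 women, 41 facilities, 500 per method overall. Assumed, because the protocol gives no uptake or trait figure by facility: the DMPA-SC share and the trait rate in two equal groups of facilities, A and B. Inside each group, choice is set to be unrelated to the trait.

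**Arithmetic.** Let the shares be sA and sB, averaging 50%, and the trait rates pA and pB.

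- Trait rate among DMPA-SC users = sA·pA + sB·pB
- Trait rate among DMPA-IM users = (1 − sA)·pA + (1 − sB)·pB
- Pooled difference = (sA − sB) × (pA − pB)

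| DMPA-SC share A/B | Trait A/B | DMPA-SC users | DMPA-IM users | Pooled difference | Within-group difference |
|---|---|---|---|---|---|
| 70/30 | 60/20 | 0.42 + 0.06 = 48% | 0.18 + 0.14 = 32% | 16 points | 0 |
| 60/40 | 60/20 | 0.36 + 0.08 = 44% | 0.24 + 0.12 = 36% | 8 points | 0 |
| 60/40 | 50/30 | 0.30 + 0.12 = 42% | 0.20 + 0.18 = 38% | 4 points | 0 |

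If either factor in the product is zero, the pooled difference is zero.

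**How often the named tests reject.** The same three settings were simulated with 41 facilities, half urban and half rural, a facility-level SD of 5 points added to both share and trait, and 600 runs each:

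| Setting | Mean pooled difference | Pooled chi-squared | Facility-clustered SE | Facility fixed effects |
|---|---|---|---|---|
| 70/30, 60/20 | 16.1 | 100% | 100% | 7.5% |
| 60/40, 60/20 | 7.8 | 72% | 68% | 5.3% |
| 60/40, 50/30 | 3.7 | 21% | 22% | 3.3% |

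Clustered standard errors leave the point estimate where it is, so they do not answer the within-facility question. The 7.5% is a little above nominal but far from 100%.

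**A second check with less structure.** A continuous trait was simulated in 41 facilities of unequal size, with a trait intraclass correlation of 0.02 to 0.20, an SD of 0.5 to 1.5 for the facility log-odds of uptake, and 1,500 runs per setting.

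- Facility uptake and facility trait level uncorrelated: the pooled t test rejects in about 5% to 27% of runs. The expected difference is zero here, so the excess comes from treating women in one facility as independent.
- Correlated at 0.5: about 10% to 83%. Here the difference itself shifts.
- Within-facility comparison: about 4% to 6% throughout.
- Equal uptake everywhere, or a trait that does not vary by facility: the pooled test stays near 5%.

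**Precision cost of stratifying.** 1,000 / 41 is about 24 women per facility. The information on the contrast is about 1,000 × 0.25 = 250 pooled, against (1,000 − 41) × s(1 − s) within facilities. That is 959 × 0.24 = 230 for shares of 60/40 and 959 × 0.21 = 201 for 70/30. Intervals widen by √(250/230) = 1.04 and √(250/201) = 1.11, before any gain from smaller trait variation within facilities. More uneven uptake would cost more.

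**The case against.** The strongest reply is that the objective is descriptive. If DMPA-SC users are more often educated or rural because uptake was higher where such women attend, that is a true feature of the user profile, and the pooled difference is the right quantity. This stands. A reader might infer that the pooled result is biased, but it is so only for a within-facility quantity that the protocol never states as its target. A reader might also infer that a facility pattern will be reported as a determinant of choice or as an effect of the product. The article says only that the groups will be compared, so that inference is not supported either.

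It is equally tempting to make the within-facility estimate the sole basis for inference. That would go too far. Facility strata absorb district of the facility, ownership and facility type entirely, and much of urban or rural location and access. Those are part of what the study wants to learn when it asks where self-injection may help.

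Two more replies have force. Every magnitude is assumed, and the mildest setting gives 4 points. Common three-day training, supervision and monitoring of counselling may also hold down facility differences in experience, though they do not make the facilities' clients alike.

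Finally, this is a condensed article, and a fuller plan may hold adjusted versions. That is possible. But the article does not leave the method open: it names specific unstratified tests for a stated objective.

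**Conclusion.** The point holds as a cheap improvement to a secondary analysis, not as an error in a stated figure. As fixed, the analysis yields one contrast that serves the user-profile question but cannot say whether a difference lies between facilities or between women within them. For experiences it cannot separate facility from product. The named tests also ignore that women are grouped by facility.

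Under the assumed ranges the pooled difference is 4 to 16 points with none inside any facility. This rests on both uptake and the trait varying between facilities, and varying together. Purposive selection makes variation in the trait likely, and nothing stated prevents variation in uptake, but the protocol shows neither. If either is absent, the concern is empty. The primary comparison's sample size is unaffected.

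**What to change.** In the Data analysis section:

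- Keep the crude comparison as the description of user profiles, with facility-clustered standard errors, and use it for statements on who and where the users are.
- Beside it, report a facility-stratified estimate: conditional logistic regression of method chosen on each characteristic, or Mantel-Haenszel for categorical ones; and linear or logistic models adjusted for facility for experiences. Where sites are sparse, stratify by facility type within district.
- Use the within-facility estimate for statements about individual choice or about differences in experience between methods.
- Report the DMPA-SC share by facility type, so that readers can see whether uptake varied at all.

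The change is to analysis wording only. Women are enrolled by health workers at the facility, so the stratum should already be known.

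The downsides are modest. Facilities where all enrolled women chose one method add nothing to the within-facility estimate. Its intervals are somewhat wider, by about 4% to 11% in the settings above. Later experience data will be thinner, at about 18 women per facility with 75% retention (750 / 41). Stratifying removes confounding by facility only; individual self-selection remains, so an adjusted difference in experience is still not proof of an effect of the method.

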### Study population

All married women of reproductive age who receive family planning counseling at a participating health facility who choose and are medically eligible to receive injectable contraception will be given an option of either DMPA-IM (current health worker administered standard of care) or DMPA-SC (new administration method, with option for self-injection after completing training). As Fig. 1 shows, those opting for DMPA-SC will receive training on self-injection procedures and an opportunity to practice injection procedures on a model (e.g. condom filled with salt) to demonstrate confidence and competency. The health worker will assess client competency using a standardized checklist; if it is demonstrated, the client will be given the opportunity to inject herself under the supervision of a health worker during the visit. If competency is not demonstrated, or the client does not feel confident enough to self-inject, the health worker will administer the DMPA-SC injection. Both clients that demonstrate competence, and clients who do not demonstrate competence or are lacking confidence to self-inject but remain interested to do so will then be shown how to use a calendar to determine when their next injection is due. Each client will receive a take-home packet that includes an Urdu-language calendar, a pictorial job aid booklet illustrating and the steps for self-injection, safe and appropriate storage, and disposal (Additional file 1), plus three units of DMPA-SC. The job aid booklet also includes a link and QR code that brings users to an animated video demonstrating the same so that they can review self-injection steps at their own time and pace at home. DMPA-SC users will also be advised that they can seek support from community health workers to learn and practice self-injection techniques, and/or seek assistance with administration of their next dose if they still do not wish to self-inject.

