### Cohort intake (Tool A) and follow-up (Tool B)

Structured intake interviews will be conducted within two weeks of enrollment. For participants indicating a preference for telephone contact, up to three attempts will be made to make each contact. Participants who indicated a preference for conducting interviews in person, as well as those that could not be reached via telephone and consented to home visits if needed, will be visited at home. Up to three attempts will be made to find a participant in their community. If participants cannot be reached after three attempts via telephone and/or three attempts in person, they will be considered ‘lost to follow up’ and dropped from the study cohort.

Approximately 120–130 days following the date each participant received/administered their contraceptive injection at the health facility and enrolled in the study, participants will be contacted for a follow-up interview (interview #2) using Tool B. This window reflects the expected period of time by which a subsequent injection would have taken place, if conducted within the effective window for DMPA (up to two weeks earlier or four weeks later than the targeted three-month reinjection date), During each follow-up interview, participants will be asked if they received (DMPA-IM) or received/administered another contraceptive injection (DMPA-SC) within the last month. If yes, the study staff will document the date the injection occurred and proceed with the interview on their experiences. If no, the study staff will proceed with questions on discontinuation, and the participant will be dropped from the study cohort.

Approximately 120–130 days following the date each participant reported receiving/administering a second contraceptive injection, they will be contacted for another follow-up interview (interview #3) and the same procedures followed. Similarly, approximately 120–130 days following the date each participant reported receiving/administering a third contraceptive injection, they will be contacted for a final follow-up interview (interview #4) and the same procedures followed. At the end of the interview, participants will be thanked for their participation and informed that the study is completed, and they will not be contacted again.

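### Women choose their own arm, yet the only method stated for comparing 12-month continuation between arms is unadjusted Kaplan–Meier, so the stated difference mixes method effect with self-selection.

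*Protocol article*

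**What the plan says.** Study design: "This will be a non-randomized prospective cohort study". Under Study population, eligible women "will be given an option of either DMPA-IM (current health worker administered standard of care) or DMPA-SC", so the client decides her arm. The abstract gives the primary objective as the comparison of 12-month continuation between the two groups.

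The Data analysis section makes three relevant statements:

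- Continuation in the two groups "will be compared at each follow-up point (6,9 and 12-month continuation rates) using Kaplan–Meier survival analysis methods".
- In the same sentence, "factors associated with risk of discontinuation analyzed using a Fine-Gray subdistribution hazard model".
- "Characteristics (e.g. demographics, contraceptive history, reasons for methods choice, reproductive empowerment measured using a validated scale" and general self-confidence are listed as participant characteristics. With participants' experiences, they "will be compared using *t* tests for continuous variables and chi^2^ tests for categorical variables".

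On timing, Participant recruitment and enrollment has women enrolled after they have received their method, and the intake section adds: "Structured intake interviews will be conducted within two weeks of enrollment".

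The end of the Background expects the user profiles of the two methods to differ and expects some factors to help or hinder continuation. The Discussion speaks of the potential of DMPA-SC to improve continuation. The limits on scope that it gives are married women only and facility-based recruitment; self-selection into arms is not mentioned.

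**The concern.** Women who opt to learn self-injection and take doses home may differ from women who opt for an injection by a health worker in ways that also affect whether they continue. Kaplan–Meier curves by arm do not remove such differences unless they are weighted or stratified, and neither is stated. The t tests and chi-squared tests would show imbalance but do nothing to the estimate of the arm difference.

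At stake is the interpretation of the primary result. The Background addresses provincial decision-makers weighing a product with a higher unit price. A crude difference could show them a benefit that reflects who chose DMPA-SC, or hide a real one.

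**Working it through.** **The plan's own figure.** Inputs from Study design: 50% continuation on DMPA-IM, a 10% difference (read as 10 percentage points, so 60%), 80% power, alpha 0.05 (two-sided assumed), equal groups, 75% retention, 500 per group.

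- Unpooled formula: (1.960 + 0.842)² × (0.5×0.5 + 0.6×0.4) / 0.10² = 384.6 per group; 384.6 / 0.75 = 513.
- Pooled-variance formula: 388 per group; 388 / 0.75 = 518 after rounding up.
- Power with 500 × 0.75 = 375 retained per group: 78.7%.

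The stated 500 is reproduced to within about 4%. The point below does not depend on an error in it. The figure is that of a crude two-group comparison, with no allowance for adjustment.

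**Bias of the crude contrast.** Suppose the method has no effect and one binary characteristic shifts 12-month continuation by e points in both arms. Continuation in an arm is then a + e × (prevalence of the characteristic in that arm), so

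spurious difference = (prevalence gap between arms) × e.

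The documents give neither quantity, so the values below are assumptions. The last column is the chance of a significant crude difference with no true effect: two-sided 5% test, 375 per arm, DMPA-IM at 50%, bias favouring DMPA-SC.

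| Prevalence gap | Effect on continuation | Spurious difference | Share of 10-point target | Chance of a significant result |
|---|---|---|---|---|
| 10 points | 10 points | 1 point | 10% | about 6% |
| 20 points | 20 points | 4 points | 40% | about 20% |
| 30 points | 25 points | 7.5 points | 75% | about 54% |

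For the last row: the null standard error is √(2 × 0.5375 × 0.4625 / 375) = 0.0364, so the critical difference is 1.96 × 0.0364 = 0.0714. The standard error under 50% against 57.5% is 0.0363, and Φ((0.075 − 0.0714) / 0.0363) = Φ(0.10) = 0.54.

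**Other direction.** If the characteristic more common among DMPA-SC choosers lowers continuation, the sign reverses. A true 10-point benefit with 4 points of adverse bias appears as 6 points. The crude test then detects it about 38% of the time (50% against 56%, 375 per arm), not 78.7%.

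**Cost of adjusting.** If covariates explain a share R² of arm choice (assumed), the variance of the adjusted difference rises by 1 / (1 − R²), equivalent to 375 × (1 − R²) per arm:

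- R² = 0: 375 per arm, power 78.7%
- R² = 0.1: 337.5 per arm, power 74.4%
- R² = 0.2: 300 per arm, power 69.3%

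**The case against.** The best defence is the Fine-Gray model. It is regression on the same outcome, study arm is an obvious term for it, and covariate lists are commonly left to an analysis plan that is not shown here. A reader might infer that no adjusted arm comparison is planned at all. The document does not support that: it is silent on whether arm enters the model, and such a model could hold arm and covariates together. What remains is that the article assigns the model to a different question, and a subdistribution hazard ratio would not by itself give the 12-month rate difference that the study is powered on. The method that is stated for the arm comparison is crude. That is a stated choice, not an omitted detail.

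It can also be said that the objective only compares two groups of choosers, that the study is labelled observational, and that crude curves describe those groups correctly. They do, and they should be kept. But the Study design section calls the arms intervention groups and the Discussion speaks of improving continuation, which is language about an effect.

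Two further inferences go too far. One is that every confounder needed is already collected. Tool A is in an additional file that is not shown; demographics and contraceptive history are named in the Data analysis section, while wealth, distance and fertility intention are not named as intake items. The other is that the bias must be most of the target effect and must favour DMPA-SC. Both size and sign rest on assumptions, and weak confounding gives about 1 point.

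**Conclusion.** The point stands in this form: women select their arm, and the only method that the article ties to the 6-, 9- and 12-month comparison makes no adjustment. Followed as written, the stated 12-month difference cannot separate the method from the women who choose it.

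The size is not known from the documents. For a single assumed binary confounder it runs from about 1 to 7.5 points over the values shown, against a 10-point target, and could go either way. Several confounders acting together could add up or offset each other. Because the plan itself expects the user groups to differ, this should be settled before the arms are compared.

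**What to change.** In the Data analysis section:

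1. Make the main 12-month comparison a covariate-adjusted risk difference with its confidence interval, for example from propensity-weighted survival curves or by standardisation from a discrete-time model. Report 6 and 9 months in the same way.
2. Name the adjustment set: characteristics fixed before method choice that Tool A actually records (demographics and contraceptive history, with others added after checking the tool), plus facility type and district.
3. Leave the empowerment and self-confidence scores out of the main set. Intake follows training and the first injection, by up to two weeks from enrollment, so these scores may already reflect exposure. Treat reasons for method choice with the same caution.
4. Keep crude Kaplan–Meier curves as description.
5. State whether study arm is in the Fine-Gray model and what that model is for.
6. Add self-selection to the limitations, with a statement that adjustment leaves residual confounding by unmeasured characteristics.

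The cost is plan wording, modest programming and a check of the intake tool. Precision falls: under the assumed R² of 0.1–0.2, power goes from about 79% to about 74–69%, and the plan should say so. No extra enrolment is proposed.

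### The named t and chi-squared tests assume independent women, and no continuation analysis is stated to allow for the 41 recruiting facilities; the likely effect on the arm comparison is modest

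*Protocol article*

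**What the plan says.** On recruitment, the Study setting and site selection section states: "A total of 41 health facilities were selected as study sites across two districts of Punjab". Facilities were chosen on purpose to differ in urban or rural location, ownership and type. Staff at these facilities counsel the women, give injections and coach self-injection. Each eligible woman is offered both injectables at her facility, so both arms can occur in one facility. Facility sizes will differ: "Enrollment limits proportional to average family planning client caseload will be set for each facility type".

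On analysis, the Data analysis section names t tests and chi-squared tests for comparing characteristics and experiences between arms, Kaplan–Meier methods for continuation at 6, 9 and 12 months, and "factors associated with risk of discontinuation analyzed using a Fine-Gray subdistribution hazard model". It mentions no facility term, cluster-robust variance, frailty or stratification for these analyses. It does not list the factors in the regression model.

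On sample size, the Study design section aims to "detect a 10% difference in 12-month continuation rates between DMPA-SC and DMPA-IM users", "with 80% power at 0.05 level of statistical significance". It mentions no design effect.

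**The concern.** Women at one facility share providers, counselling, commodity supply and catchment area. Their characteristics, experiences and continuation may therefore be more alike than those of women from different facilities. If the DMPA-SC share also varies between facilities, an analysis that ignores facility understates the standard error of the arm difference, and the real type I error exceeds the nominal 0.05. This bears on the primary comparison of 12-month continuation and on the secondary comparisons of characteristics and experiences. A factor that varies only between facilities is informed by 41 units rather than by about 750 retained women, so it is the most exposed.

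**Working it through.** **Inputs from the protocol article.** Study design: 0.05 level, 80% power, a 10-point difference, "a 12-month continuation rate of 50% for DMPA-IM users", "Assuming equal preference for each injectable method" (1:1 arms), "a retention rate of 75% follow-up following the 4th injection", and 500 women per group. Site selection: 41 facilities. A two-sided test is assumed, because sidedness is not stated.

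**Assumed inputs, not in the document.** Clustering of method choice by facility, ρx = 0.1–0.3. Clustering of continuation by facility (ICC), ρy = 0.02–0.05.

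**Step 1: the plan's own figure.** With unpooled variance, n = (0.5×0.5 + 0.6×0.4) × (1.960 + 0.8416)² / 0.10² = 0.49 × 7.849 / 0.01 = 384.6, so 385 evaluable per arm, and 385/0.75 = 513.3, so 514 enrolled. The pooled formula gives 388, and 388/0.75 gives 518. With 500 × 0.75 = 375 retained per arm, power is 78.7%. The stated 500 is thus a rounded figure for independent women. A one-sided test would need only 305/0.75, or 407, which would leave room for a design effect of 500/407 = 1.23, but the article mentions neither.

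**Step 2: women per facility.** Enrolled: 1,000/41 = 24.4. Retained: 750/41 = 18.3. The retained number is the one that matters for 12-month continuation.

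**Step 3: the arm contrast.** Variance inflation = 1 + (m − 1)ρxρy.

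| Comparison | m | Low end (ρx 0.1, ρy 0.02) | High end (ρx 0.3, ρy 0.05) |
|---|---|---|---|
| 12-month continuation | 18.3 | 1 + 17.3×0.002 = 1.03 | 1 + 17.3×0.015 = 1.26 |
| Intake characteristics, same assumed ρ | 24.4 | 1 + 23.4×0.002 = 1.05 | 1 + 23.4×0.015 = 1.35 |

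For continuation the standard-error ratios are √1.035 = 1.017 and √1.259 = 1.122, so intervals are 1 − 1/1.017 = 2% to 1 − 1/1.122 = 11% too narrow. For intake characteristics the ratios are 1.023 and 1.162, so 2–14% too narrow.

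**Step 4: how far this depends on the spread of the DMPA-SC share.** If v is the between-facility variance of the share actually observed (mean one half), and a facility effect acts equally on both arms, then the design effect is (1 − ρy) + 4v·m·ρy. With ρy = 0.05 and m = 18.3:

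| SD of share | Design effect | Type I error of an unadjusted test |
|---|---|---|
| 0 | 0.95 | 0.044 |
| 0.1 | 0.99 | 0.048 |
| 0.2 | 1.10 | 0.061 |
| 0.3 | 1.28 | 0.083 |

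This agrees with Step 3 when 4v = ρx + (1 − ρx)/m. With ρx = 0, 4v = 1/18.3 = 0.055, the SD is √(0.055/4) = 0.117, and the design effect is 1. Values below 1 therefore need observed shares more even than chance alone would give.

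**Step 5: a facility-level factor (ρx = 1).** 1 + 17.3×0.02 = 1.35, and 1 + 17.3×0.05 = 1.86. Unequal facility sizes raise this. With an assumed coefficient of variation of 0.6, 1 + (1.36×18.3 − 1)ρy is 1.48–2.19.

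**The case against.** The strongest reply is that a condensed article is silent here and has not decided anything. It names methods in two sentences and leaves the variance estimator to an analysis plan that is not shown. A Fine-Gray model can take a cluster-robust variance, and Kaplan–Meier point estimates do not depend on that choice. This stands for those two methods: the document does not say that they will treat women as independent. It does not answer the point for the t and chi-squared tests, which are named outright and assume independence, or for the sample size, which matches a calculation with no design effect.

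A second reply is that both methods are offered in each facility, so a shared facility effect largely cancels. That stands as a limit on size (Step 4). It is less secure if facility acts mainly on one arm. DMPA-SC women take three units home, while DMPA-IM must be given by a health worker. As an illustration, assume an ICC of 0.05 in the DMPA-IM arm only, equal shares, and 18.3/2 = 9.1 retained DMPA-IM women per facility. That arm's design effect is 1 + 8.1×0.05 = 1.41, the contrast's is (1.41 + 1)/2 = 1.2, and the type I error is about 0.07.

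A third reply is that the model's facility-level factors are never named. That also stands. The figures in Step 5 are conditional on such factors being entered.

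**Conclusion.** The concern holds in limited form. The plan names tests that assume independence for women recruited through 41 deliberately varied facilities, and states no allowance for facility in the continuation analyses. For the arm contrast in continuation, variance inflation is about 1.03–1.26, with intervals about 2–11% too narrow, and it may be at or slightly below 1 if the DMPA-SC share is constant. A facility-level factor, if used, has a design effect of about 1.35–1.86. These figures rest on assumed clustering, since the document gives neither the ICC nor the spread of the DMPA-SC share, and on the planned 75% retention.

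Three stronger readings are tempting and not supported:
- A reader might infer that every planned analysis treats women as independent and that its standard errors and P values are wrong. The article states no variance estimator for the Fine-Gray model, and the size and even the direction of the error depend on quantities that are not given.
- A reader might apply the full design effect to the arm comparison. At an ICC of 0.05 that would mean power of 52% and a type I error of 0.151. It requires each facility to supply only one arm, whereas both methods are offered to each woman.
- A reader might expect clustered errors to deal with confounding by facility. They correct precision only, and confounding is a separate problem of this non-randomized comparison.

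**What to change.** State in the plan that facility is the cluster for robust (sandwich) or cluster-bootstrap errors in the continuation comparison, the Fine-Gray model, and the arm comparisons of characteristics and experiences. For the last of these, replace the plain t and chi-squared tests with regressions on arm that use facility-clustered errors. Stratify the continuation comparison by facility type and district. Report the observed ICC of continuation and the spread of the DMPA-SC share across facilities, and show power over a range of ICCs, so that readers can see how much the adjustment mattered.

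The cost is a sentence or two in the plan and an option in the software. No further data are needed if facility, type and district are kept in the dataset. Intervals may widen slightly. Stratification reduces confounding by facility type and district but does not remove confounding by individual facility.
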